### Eligibility criteria

#### Inclusion criteria

Eligible participants can be included if they meet the following criteria:
Employed at the DVLA and aged 18 to 70.Understand written and spoken English or Welsh.

#### Exclusion criteria

None.

### Employment as usual

The DVLA currently provides training courses on mental health, flexible working hours, confidential help lines, advice and a short term counselling service. This includes a 24-h Employee Assistance Programme providing confidential help and advice. DVLA also engage with organisations such as Public Health Wales and Time to Change Wales to provide a program on managing mental health issues, including a ‘brief intervention’ for alcohol problems and advice and guidance on coping with bereavement and train mental health champions to support staff experiencing mental health difficulties. Education and support is also provided by the Dementia Friends and Carers Associations, alongside the provision of an Occupational Health program.

### Procedures

Data will be collected from employment records, and by paper questionnaires handed out to individuals at the appropriate time points during the RCT evaluation (before commencement of the intervention, post Prevail-Staff and Prevail-Manager intervention programmes, and at 12 months follow-up). Data will be collected in three waves.

#### Wave 1

This will occur 1–2 weeks prior to the Prevail intervention for the Active group, with data collection for the Control group being yoked to this (but with participants and researchers being blind to which group each cohort of participants are in). Its aim is to provide baseline measures of levels of stigma and help-seeking behavior, and information about current well-being and psychological function.

#### Wave 2

This will occur approximately 4 weeks after the participant has engaged in the Prevail intervention for the Active group, with data collection for the Control group being yoked to this. Its aim is to examine if the Prevail intervention is able to change attitudes about mental health, improve help-seeking, and improve psychological well-being and levels of function.

#### Wave 3

This will occur 12 months after the Prevail intervention for the Active group, with data collection for the Control group being yoked to this. Its aim is to examine if any gains shown following engagement with the Prevail intervention in attitudinal change, mental health, and well-being are able to be sustained over a 12-month period and if the Prevail programme is able to decrease levels of absenteeism and presenteeism.

#### Registered sick leave

Sick leave will be assessed in two ways. Our primary measure of sick leave will be records kept by the Human Resources department of the DVLA. Days of sick leave in the 12 months pre and post the Prevail intervention programme for employees in the Active intervention and EAU Control groups will be coded into “mental health reasons”, “physical health reasons” or “other” by raters blind to the group assignment of the employees.

### Secondary outcome measures

#### Self-reported sick leave

Self-reported sick leave will be assessed by asking about staff members’ estimated total number of days sick leave in the last 12 months on a seven-point scale (none, 1, 2–3, 4–10, 11–20, 21–30, 30+) and this will be repeated for sick leave separated into absences due to physical health reasons and absences due to mental health reasons.

#### Work performance/Presenteeism

Self-reported work performance will be assessed via an adaptation of the Health and Work Performance Questionnaire (HPQ [19];) using a four point Likert scale, ranging from 0 to 3 rating staff member’s work performance over the past year; comparisons of this to workers who do a similar job; and comparisons to the staff member’s usual performance. This will be followed by questions asking to what extent a physical health problem or a mental health problem affected their work performance. Staff will be asked if they have been mentally unwell whilst working and, if so, will be asked to repeat the previous questions but to respond specifically to their estimated work performance during the time that they were unwell.

#### Work and social adjustment scale

The WSAS [20] measures impairment in functioning due to a common mental disorder. It consists of five questions (e.g., “because of my [disorder], my ability to form and maintain close relationships with others, including those I live with, is impaired.”) that are answered on an eight-point scale (0 indicates no impairment at all and 8 indicates very severe impairment).

#### General anxiety disorder assessment-7

The GAD-7 [21] measures symptoms of general anxiety. Participants rate how often they have been bothered by the seven problems (e.g., “Trouble relaxing.”) over the past 2 weeks on a four-point scale (not at all, several days, more than half the days, nearly every day).

#### Patient health Questionnaire-9

The PHQ-9 [22] measures the severity of depression. The PHQ-9 is a nine item depression scale based on the diagnostic criteria for major depressive disorder. Participants rate how often they have been bothered by the nine problems listed (e.g., “Poor appetite or overeating.”) over the past 2 weeks on a four-point scale (not at all, several days, more than half the days, nearly every day).

#### Kessler psychological distress scale (K6)

The K6 [23] is a non-specific distress scale used as a screen for severe mental distress Participants self-report 6 symptoms: felt nervous, hopeless, restless and fidgety, worthless, depressed, and that everything was an effort. Each question is rated on a scale of ‘none of the time, a little of the time, some of the time, most of the time, all of the time’ (with scores of 0–4 being awarded to each respectively). Responses to the 6 items of the K6 are summed to yield a score of 0–24. Severe mental distress is defined as a K6 score of > = 13.

#### EQ-5D-5 l

The EQ***-***5D-5 L [24] is a generic measure of health status which defines health in terms of five dimensions: mobility, self-care, usual activities, pain or discomfort, and anxiety and depression. For each of the five items five descriptions are offered (e.g., I have no problems washing of dressing, to I am unable to wash or dress myself). Participants rate which description best describes their health today.

### Evaluation of ethical issues

#### Randomization

The study has a two-armed cluster randomised design that takes place at the level of the managers within the organisation. Managers will be randomly allocated into the Active intervention group or the Control group (EAU) by computer-generated random numbers. The randomisation will be stratified at the level of division within the DVLA and gender of the manager (man vs. woman) so that we achieve a similar profile of managers in each arm of the study.

#### Blinding

This study will involve a cluster-randomisation design. The employees will be randomised before they give informed consent as they will be allocated to the Control or Active intervention group depending on if their manager has been allocated to the Control or Active groups. Given the nature of the intervention it will be impossible for the managers or the employees to be blinded as to which group they are in, although the pre-evaluation assessments using psychometric tests were completed blind to group allocation (with both the researchers and the employees being blind to this). Data analysis (e.g., evaluation of number of days sick leave taken, scoring of psychometric measures) will be done by a member of the research team who will be blind as to the group allocation of the employee.

### Data analysis

Statistical analyses adapted for cluster-randomised controlled trials will be used with random effect logistic regression (for binary data) and linear regression (for continuous data) (see [25]). Should potential confounders prove to be unevenly distributed, we will adjust for these in the regression model (e.g., gender).

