### Recruitment and consent

Eighty managers across four divisions of the DVLA will be chosen by the DVLA to take part in the study on the basis of workload considerations. All managers will be given information about the aims and objectives of the study and will be asked by the DVLA to take part. However, participants will be blind as to whether they will be in the Prevail or Employment as Usual (EAU) group. These 80 managers will be managing approximately 960 employees.

Prior to the commencement of the Prevail intervention programme, managers and employees will be invited to a pre-intervention information session to explain the aims of the Prevail programme and be told that they have been selected as possible candidates for this psychological intervention. At this pre-session all participants (employees and managers) will be invited to complete the baseline evaluation measures. Completion of the baseline measures is voluntary and written informed consent will be taken at this time for those that wish to participate in the study and complete the evaluation measures. All participants and researchers are blind at this stage to as whether they are to be allocated to the Prevail (Active) group of Employment as Usual (Control) group. Any employees and managers who do not wish to participate in the research project will be free to leave the pre-intervention session without the need to justify their decision.

The 80 managers will then be allocated to the Active or Control arms of the study. Allocation will be random, but stratified by division and by the gender of the manager to ensure equal numbers within Active and Control groups across these variables. For managers and their teams in the Active arm of the study, the DVLA has mandated the Prevail intervention programme as part of their work commitments, but the evaluation of outcomes of this via the cluster RCT was not mandated.

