### Randomisation

The randomisation will take place at the level of managers (*N* = 80). Managers will be stratified by division of the DVLA [Information Technology Services (ITS), the Contract Centre (CC), Casework and Enforcement Group (CAEG), and Input Services Group (ISG)] and by the gender of the manager. This is to ensure that these variables are equally distributed across the two arms of the study. A computer-generated random sampling procedure will be used to ensure unbiased allocation to each group: https://www.sealedenvelope.com/.

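### The only covariate rule adjusts on observed imbalance, so it would normally leave out the stratification factors and admits the Wave 1 score only if it looks uneven

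*Protocol article*

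**What the plan says.** All places are in the protocol article.

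- **Data analysis.** The models are "random effect logistic regression (for binary data) and linear regression (for continuous data"), in forms suited to cluster trials. The only statement on covariates is "Should potential confounders prove to be unevenly distributed, we will adjust for these in the regression model (e.g., gender"). It does not say what counts as uneven, which variables are candidates, or whether gender means the employee's or the manager's.
- **Recruitment and consent.** "Allocation will be random, but stratified by division and by the gender of the manager to ensure equal numbers within Active and Control groups". The Randomisation section repeats this ("Managers will be stratified by division of the DVLA") and gives the reason: "This is to ensure that these variables are equally distributed across the two arms of the study".
- **Procedures, Wave 1.** "Its aim is to provide baseline measures of levels of stigma and help-seeking behavior, and information about current well-being and psychological function". The Recruitment and consent section makes completion voluntary.
- **Registered sick leave.** The HR measure covers "Days of sick leave in the 12 months pre and post the Prevail intervention programme". The Recruitment and consent section lets these data reach the researchers only as group summaries.

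**The concern.** A covariate earns its place in a trial model by predicting the outcome, not by differing between arms. The stated rule uses the second criterion, and this sits badly with the design in two ways.

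First, the randomisation is stratified so that division and manager gender will be balanced. A rule triggered by imbalance would therefore normally pass over the two factors the design used. The standard error then ignores the between-stratum variation that stratification has already removed from the comparison.

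Second, Wave 1 measures the same scales as the follow-up waves. A person's earlier score is likely to be a strong predictor of the later one, yet it enters only if the arms happen to differ on it.

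Because neither the trigger nor the candidate list is defined, the primary model is settled only after the data have been inspected. At stake are efficiency and a fixed primary analysis.

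**Working it through.** **1. The article's own figure.** Inputs from Statistical power: alpha 0.05, power 80%, standardised effect 0.30, cluster size 12, ICC 0.05. The two-sided normal formula gives 175 per group. Design effect = 1 + (12 − 1) × 0.05 = 1.55. Then 175 × 1.55 = 271.25 per group, or 542.5 in total. The stated 271 and 542 reproduce. They contain no allowance for covariate adjustment.

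**2. Always adjusting for baseline.** For a continuous outcome the variance is multiplied by 1 − r², where r is the baseline/follow-up correlation at the level of the cluster mean. The article gives no r, so 0.3 to 0.7 is assumed.

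| r | 1 − r² | Sample-size equivalent, 1/(1 − r²) | n per group, 271.25 × (1 − r²), rounded up | Unadjusted SE / adjusted SE | Power at 271 per group |
|---|---|---|---|---|---|
| 0.3 | 0.91 | 1.10 | 247 | 1.05 | 84% |
| 0.5 | 0.75 | 1.33 | 204 | 1.15 | 90% |
| 0.7 | 0.51 | 1.96 | 139 | 1.40 | 97.5% |

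Unadjusted power at 271 per group is 80%.

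**3. What the imbalance trigger recovers.** Cluster means were simulated with 23 clusters of 12 per arm and 40,000 runs. Baseline was adjusted for only when its difference between arms had p < 0.05. That threshold is an assumption, since the article states none.

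| r | Power, never adjusting | Power, trigger | Power, always adjusting | Type I error, trigger | Adjusted and unadjusted disagree on significance (true effect 0.30) |
|---|---|---|---|---|---|
| 0.3 | 79.5% | 79.6% | 82.0% | 4.8% | 7% |
| 0.5 | 79.2% | 80.1% | 88.7% | 4.4% | 13% |
| 0.7 | 78.7% | 80.6% | 97.0% | 3.5% | 19% |

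The trigger fires in about 5% of trials, so it recovers little of the gain. Simulated power is slightly below step 2 because it uses t tests on cluster means.

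**4. Leaving out the strata.** Suppose division and manager gender explain a share g of the between-cluster variance (assumed; not in the article). The variance factor is v = 12 × 0.05 × (1 − g) + 0.95, against 1.55 without adjustment. Required n per group is 175 × v. The actual type I error of a nominal 5% test that ignores the strata is 2 × [1 − Φ(1.96 × √(1.55/v))].

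| g | v | n per group | Power if adjusted, 271 per group | Type I error if ignored |
|---|---|---|---|---|
| 0.10 | 1.49 | 261 | 82% | 4.6% |
| 0.25 | 1.40 | 245 | 84% | 3.9% |
| 0.50 | 1.25 | 219 | 88% | 2.9% |

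**5. Planned size.** With 480 per group and no losses, unadjusted power is about 96%.

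**The case against.** **The article does not exclude these covariates.** It is a short journal text, and a full covariate list may stand elsewhere. This is right as far as it goes: a reader might infer that baseline scores and strata will never be adjusted for, and the text does not say so. But the article does print a rule, and a later plan must either follow it or contradict it. The criticism is of that rule.

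**The strata could still trigger adjustment.** Stratification balances managers, while outcomes are analysed on employees. Team sizes vary and completion is voluntary, so division or manager gender may be uneven among those analysed. This stands, and it is why the claim is that the rule would *normally* omit them.

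**Imbalance need not be chance.** Consent is sought again at Waves 2 and 3, when participants know their arm, so differential response can unbalance the analysed sample. This also stands. It is a reason to keep imbalance-based adjustment as a sensitivity analysis, but it does not justify letting an undefined trigger choose the primary model.

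**Analysis is blind to allocation** (Blinding section). That limits deliberate steering. It supplies no threshold and recovers no precision.

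**The trial has sample size to spare.** About 96% power assumes no losses. The Statistical power section expects many unusable records and also assigns part of the surplus to comparisons by mental health history. The objection does show that the loss need not leave the trial underpowered.

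**Baseline is not available for everyone, and HR data are not individual.** Both are correct, and both limit the remedy.

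**Conclusion.** The point holds as a matter of efficiency and prespecification. The stated rule would normally omit the stratification factors and admits the Wave 1 score only on visible imbalance, with nothing to say when that is met.

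For continuous outcomes, always adjusting for baseline is worth about 1.10 times the sample size at r = 0.3 and 1.96 times at r = 0.7. These sizes rest on an assumed r, and the stratum figures on an assumed g. The direction holds for any appreciable r or g. For logistic models the gain is in power for the conditional odds ratio, not in a smaller standard error.

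A reader might infer that a data-driven rule inflates the type I error. That is not shown: with one candidate covariate and a fixed threshold the simulated error was 3.5% to 4.8%, and ignoring the strata gave about 2.9% to 4.6%, all below the nominal 5%. An open list and threshold leave room for selective choice, but no inflation was computed. A reader might also extend the point to an individual-level model for HR sick leave; the group-level data flow does not permit one. The change should be made, but validity is not in question.

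**What to change.** For the SASS and the other questionnaire outcomes, replace the imbalance sentence with: *Each model includes arm, the Wave 1 value of the same outcome, division and manager gender as fixed effects, and manager/team as a random effect, whatever the observed balance. Adjustment for other variables found to be imbalanced is a sensitivity analysis.*

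Three additions make it workable:

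- State how participants without a Wave 1 score are retained, for example by a missing indicator or imputation, since Wave 1 is voluntary.
- Link waves by a non-identifying study and team code on each questionnaire. This is compatible with the Data management section, which keeps personal information off the forms.
- For HR sick leave, apply the same adjustment (prior 12-month days, division, manager gender) only if HR runs the model or supplies de-identified individual records. Otherwise state that the adjustment does not apply to that outcome.

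The cost is a few sentences in the analysis section, the linkage code and the handling of missing baseline values. No new questionnaire measure is needed for the questionnaire outcomes. The HR extension needs a change to the data arrangement.

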### Statistical power

Our cluster size is determined by the management structure of the DVLA, with each manager managing around 12 employees. A normal (non-clustered) RCT power analysis with parameters of alpha = 0.05, power of 80%, and standardised effect size of 0.30 (small effect size [26]) requires 175 per group (*N* = 350). To account for the reduction in power due to clustering we assumed an average cluster size of 12, and an intra-cluster correlation coefficient (ICC) of 0.05 and this leads to a design effect of 1.55 [27]. Hence, we require a sample size of around 271 per group (*N* = 542). Our chosen sample size (*N* = 960) exceeds this by around a factor of two as we anticipate that many employees’ data may be invalid for final data analysis due to staff leaving their current DVLA team, or not consenting to complete the psychometric measures over the three waves of evaluation (i.e. pre-Prevail, post-Prevail, and 12-months follow-up). It also allows for supplementary statistical analyses on the effectiveness of Prevail, such as a comparison between the two arms of the study for employees with a previous history of mental health problems and those without. It would by hypothesised that the effects of Prevail would be more impactful for those employees with mental health difficulties than for those employees with no such history.

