For the two follow-up data collection waves: post-Prevail (termed wave 2) and 12-month follow-up (termed wave 3), the DVLA will mandate that staff in both the Active and Control arms of the research design attend follow-up sessions. At these sessions, participants will be briefed as to the progress of the Prevail intervention trial and will be invited to complete the psychometric measures as evaluation of the intervention programme. Once again, completion of the measures is voluntary and written informed consent will be taken at this time for those that wish to participate in the evaluation. Those participants who do not so wish are free to leave prior to completion of the psychometric measures.

Data from Human Resources (HR) records for the staff and managers in the study will be processed by the DVLA Human Resources staff. This data will only be communicated to the researchers at a group level (e.g., average number of sick days in the Prevail group as compared to the Control group over the last 12 months), separated by gender and age, etc., in order to ensure that the sickness absence data is anonymous to the research team. If the group size for any specific data (e.g., average number of sick days in the Prevail group over the last 12 months for females aged 60+, etc.) falls below an N of 10 this data will not be communicated to the research team in order to protect the identities of the staff group.

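### The sample-size section forecasts that data from staff who leave their team may be invalid, and nothing in the protocol article secures analysis as randomised

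*Protocol article*

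**What the plan says.** **Statistical power.** The calculation uses "parameters of alpha = 0.05, power of 80%, and standardised effect size of 0.30", which "requires 175 per group". For clustering, "we assumed an average cluster size of 12, and an intra-cluster correlation coefficient (ICC) of 0.05". The resulting inflation factor of 1.55 brings the requirement to about 271 per group, 542 in total. The chosen 960 is explained by an expectation that many employees' "data may be invalid for final data analysis due to staff leaving their current DVLA team", or lost through staff "not consenting to complete the psychometric measures over the three waves of evaluation". The same paragraph gives the surplus another use: supplementary analyses, such as comparing the arms in staff with and without a history of mental health problems.

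**Data analysis.** Random-effect logistic and linear regression are named, with adjustment for unevenly distributed confounders. The section does not say who is analysed.

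**Randomisation and Blinding.** Managers are randomised and employees take their manager's allocation. After baseline, managers and employees know their arm.

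**Recruitment and consent.** DVLA mandates attendance at the follow-up sessions in both arms, but completing the questionnaires is voluntary. For sick leave, "Data from Human Resources (HR) records for the staff and managers in the study will be processed by the DVLA Human Resources staff", and the researchers receive group-level figures only.

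**Primary outcome measures.** These are the SASS and registered sick leave, the latter taken from HR records.

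**The concern.** An employee who moves to another DVLA team after randomisation still belongs to the cluster and arm allocated. That person is still employed, can be invited to Waves 2 and 3, and still has an HR record. Nothing about the move makes the data invalid.

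Moving is also not obviously independent of arm. Prevail trains managers in problem-solving and co-production, promotes work adjustments and encourages disclosure. The Intervention section itself cites evidence that managers' behaviour predicts employees' mental health. Any of these could change who leaves a team and why. Conditioning on staying would then compare stayers selected differently in the two arms, and a random-effect model or adjustment for gender would not repair that.

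The HR route makes timing important. Because researchers see only group summaries, they could not put movers back if HR had formed the groups from teams as they stood at extraction.

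**Working it through.** **1. The plan's own figures reproduce.**
- Unclustered (two-sided alpha assumed, SD = 1): n = 2(1.960 + 0.842)² / 0.30² = 174.4, so 175 per group.
- Design effect: 1 + (12 − 1) × 0.05 = 1.55.
- Clustered: 175 × 1.55 = 271.25 per group, 542.5 in total, against the stated 271 and 542.

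The issue is who is analysed, not the sample-size arithmetic.

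**2. Largest loss the plan can absorb.** 960 − 542 = 418, and 418 / 960 = 43.5%. This is a ceiling for all causes together. The article does not say how much is expected from team moves.

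**3. Power is not the problem.** At an effect of 0.30 SD:
- All 480 per arm kept: effective n = 480 / 1.55 = 309.7, power 0.962.
- 271 per arm, design effect held at 1.55: power 0.801.
- 271 per arm, clusters shrunk to 12 × 542/960 = 6.8 and design effect 1.289: power 0.868.

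**4. Possible bias on a questionnaire score (assumed inputs).** Take outcome SD 1, no true effect, and retention that follows a normal selection model with correlation ρ to the outcome. The mean among those retained shifts by ρ·φ(z)/r, where r is the fraction retained and z = Φ⁻¹(1 − r). The bias is the difference between arms. Overall retention is set at the 56.5% floor.

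| Retention, arm 1 v arm 2 | ρ, arm 1 v arm 2 | Size of bias (SD) |
|---|---|---|
| 56.5% v 56.5% | equal | 0 |
| 65% v 48% | 0.1 in both | 0.03 |
| 65% v 48% | 0.3 in both | 0.08 |
| 65% v 48% | 0.5 in both | 0.13 |
| 56.5% v 56.5% | 0.3 v 0.1 | 0.14 |
| 56.5% v 56.5% | 0.3 v 0 | 0.21 |

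**5. Effect on the error rate.** With 271 per arm and design effect 1.55, SE = √(2 × 1.55 / 271) = 0.107. The two-sided 5% error becomes about 0.075 for a bias of 0.05 SD, 0.155 for 0.10 SD and 0.46 for 0.20 SD.

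**6. Sick days, only if HR were to drop movers (assumed inputs).** Let 20% of staff average 25 days and 80% average 4, the same in both arms, so the full-roster mean is 0.2 × 25 + 0.8 × 4 = 8.2 days. Suppose 30% of high-absence controls and 20% of high-absence Prevail staff move, and 10% of the rest in each arm.
- Control stayers: (0.14 × 25 + 0.72 × 4) / 0.86 = 7.42 days.
- Prevail stayers: (0.16 × 25 + 0.72 × 4) / 0.88 = 7.82 days.

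The spurious difference is 0.40 days against Prevail. The SD of this mixture of group means is 21 × √(0.2 × 0.8) = 8.4 days, so the bias is about 0.05 SD.

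**The case against.** The strongest reply is that no exclusion rule exists. The sentence is a hedged forecast that explains a sample size, the Data analysis section excludes nobody, and analysis populations are usually left to a statistical analysis plan, which is not shown. This stands in part. A reader might infer that the plan has replaced the randomised comparison with one of stayers, and the text does not go that far. But the finding is not the mere absence of an analysis set. The article's only statement on which data are analysable names a post-randomisation event as a reason for invalidity.

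Four further limits stand:

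- **Partial completers.** A reader might infer that anyone missing one wave is discarded. The wording can be read that way but does not clearly say so. Data never given are missing data, a separate matter from calling data invalid.
- **HR sick leave.** A reader might infer that both primary outcomes are biased. HR data are described as covering the staff and managers in the study, and nothing removes leavers or questionnaire non-completers. The sick-day example in the working is therefore conditional.
- **Meaning of leaving a team.** The phrase also covers people who leave DVLA, whose later questionnaires may be unobtainable. The recoverable share is unknown.
- **Direction and size.** With no true effect, bias needs loss or selection to differ by arm. It could run against Prevail, and in the sick-day example it is small.

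**Conclusion.** The concern holds in conditional form. If acted on, the forecast would exclude randomised employees because of an event that Prevail could influence, and nothing in the article prevents this. The SASS and other questionnaire outcomes are the clearer exposure. For HR sick leave the gap is only that the roster is not secured.

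The documents do not allow the bias to be sized. The 43.5% is an upper limit on total loss, not a predicted loss of movers. The 0 to 0.21 SD range applies at that limit, covers non-response as well as moves, and rests on assumed selection. It shows that a bias could be material beside an effect of 0.30 SD, not that one will occur. Keeping movers removes only their part of it; voluntary non-response remains and needs a missing-data analysis.

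**What to change.** - Remove team-leaving as a ground for invalid data in the Statistical power section. Describe the surplus as cover for missing follow-up and supplementary analyses.
- Fix the roster at randomisation and state that every listed employee is analysed in the arm and cluster allocated, whatever their later moves.
- Invite movers who remain at DVLA to Waves 2 and 3.
- Use all available waves in the planned random-effect model, with a missing-data sensitivity analysis.
- Instruct HR, before extraction, to build its group-level summaries on the frozen roster and to report days at risk (person-time) for each group, so that those who leave DVLA count up to their leaving date. This respects the group-level release rule; a person-level offset fitted by the researchers would not.

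**Cost.** Protocol wording, one instruction to HR, and slight dilution of the contrast from staff who move between teams. Questionnaires carry no personal information, so whatever code links the waves must keep a mover tied to the original cluster. Power does not suffer: it is 0.801 at the planned minimum and rises towards 0.962 as more of the 480 per arm are kept, before any dilution.

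### The expected larger effect in staff with a mental-health history is an interaction, which separate arm comparisons do not test and which 960 employees could detect only if large

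*Protocol article*

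**What the plan says.** All of this stands in the Statistical power section of the protocol article. The calculation starts from "A normal (non-clustered) RCT power analysis with parameters of alpha = 0.05, power of 80%, and standardised effect size of 0.30" and "requires 175 per group". For clustering, "we assumed an average cluster size of 12" and an ICC of 0.05 give a design effect of 1.55, and then: "Hence, we require a sample size of around 271 per group", or 542 in total.

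The chosen 960 "exceeds this by around a factor of two as we anticipate that many employees" may yield data that cannot be used, because staff change team or do not consent at every wave. The next sentence adds a second benefit: "It also allows for supplementary statistical analyses on the effectiveness of Prevail, such as a comparison between the two arms of the study", for employees who have a history of mental health problems and those who do not. The section closes by hypothesising that Prevail will have more impact in employees with mental health difficulties than in those with no such history.

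No loss rate, history share, target difference or power is given for this comparison.

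**The concern.** The closing hypothesis is about the difference between two treatment effects. The analysis named just before it is a comparison of the arms for each kind of employee. These answer different questions. Significance in one group and not in the other is not evidence that the effects differ, because the groups differ in size and therefore in power.

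The sample size is also presented as making this analysis possible, but the calculation sizes only the overall arm comparison. An interaction is estimated much less precisely than a main effect, so a sample that is comfortable for one can be weak for the other.

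At stake is a predictable misreading. A chance split between two subgroup tests could be reported as showing whom Prevail helps. An interaction too imprecise to settle the matter could equally be taken as showing that history makes no difference.

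**Working it through.** **Inputs from the protocol article:** alpha 0.05 (two-sided, the reading that gives 175), power 80%, effect 0.30 SD, cluster size 12, ICC 0.05, 80 managers with 40 in the intervention arm, and about 960 employees.

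**Assumed here:** a history share p of 20% to 50%; equal team sizes; no gain from baseline adjustment.

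**1. The plan's own figure.** Per group, 2 × (1.960 + 0.842)² / 0.30² = 174.4, so 175. The design effect is 1 + (12 − 1) × 0.05 = 1.55. Then 175 × 1.55 = 271.25 per group, or 542. The figure reproduces.

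**2. Power for the interaction.** History varies within teams, so the team effect largely cancels:

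SE² = 4 × (1 − ICC) / [N × p × (1 − p)]

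Power for a 0.30 SD difference is Φ(0.30/SE − 1.960). The difference detectable with 80% power is 2.802 × SE.

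| Analysed | History share | SE | Power for 0.30 SD | Detectable difference |
|---|---|---|---|---|
| 960 | 20% | 0.157 | 48% | 0.44 SD |
| 960 | 30% | 0.137 | 59% | 0.38 SD |
| 960 | 50% | 0.126 | 66% | 0.35 SD |
| 542 | 20% | 0.209 | 30% | 0.59 SD |
| 542 | 30% | 0.183 | 38% | 0.51 SD |
| 542 | 50% | 0.167 | 43% | 0.47 SD |

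For example, at 960 and 50%: SE = √(3.8 / 240) = 0.126, and 0.30/0.126 − 1.960 = 0.42, which gives 66%. A generalised least squares check with history status drawn at random within teams gave an SE of 0.128 for this cell.

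For 80% power at 0.30 SD, N = 3.8 × (2.802/0.30)² / [p(1 − p)]. That is about 1,326 at a 50% share and 2,071 at 20%, both above 960.

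**3. What separate tests would show.** Suppose the effect is 0.30 SD in both groups, so there is no effect modification, and 542 are analysed. Each group has its own design effect, 1 + (n/80 − 1) × 0.05, where n is the group's total. With powers P₁ (history) and P₂ (no history), and the tests treated as independent, the chance that they disagree is P₁(1 − P₂) + (1 − P₁)P₂.

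| History share | P₁ | P₂ | Chance of disagreement |
|---|---|---|---|
| 20% | 34.0% | 80.7% | 0.340 × 0.193 + 0.660 × 0.807 = 60% |
| 30% | 46.2% | 76.5% | 0.462 × 0.235 + 0.538 × 0.765 = 52% |
| 50% | 64.6% | 64.6% | 2 × 0.646 × 0.354 = 46% |

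At a 30% share, 0.538 × 0.765 = 41% of trials would be significant only in the no-history group, the opposite of the hypothesis, although the effects are equal.

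**4. The main comparison.** 960/542 = 1.77, so a factor of two is loose. The 542 uses the design effect for 12 analysed per team. Spread over 80 teams, 542 is 6.775 per team: the design effect is 1 + 5.775 × 0.05 = 1.289, the effective number is 271/1.289 = 210 per group, and power is about 87%. Solving n = 175 × [1 + (n/40 − 1) × 0.05] gives 212.8 per group, about 426 in total. So 542 is conservative.

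**The case against.** The strongest reply is that the protocol promises nothing here. It calls the analysis supplementary, attaches no power to it, and leaves it out of the hypotheses in the Aims and hypotheses section. A sample can allow an exploratory comparison without 80% power. This stands: no stated power is breached.

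The wording is also compatible with an interaction term, the Data analysis section commits to regression adapted for clustering, and an analysis plan may specify the term. So separate tests are not certain. The sentence nevertheless names an arm comparison, states a hypothesis about a difference in effects, and offers the sample size as support, without connecting the three.

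If the hypothesis is true, the comparison within the history group has more power than a flat 0.30 SD implies. With an average effect of 0.30, a difference of 0.30 and a 30% share, the effect there is 0.30 + 0.7 × 0.30 = 0.51 SD, with power of 89% at 542 and 98% at 960. This is correct, but it shows that Prevail works in that group, not that it works better there.

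Two stronger readings are tempting and are not supported:

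- **That the surplus is spent twice.** A reader might infer that all of it is committed to loss. The protocol gives loss as the reason for the larger sample but states no rate. The 43.5% loss that would bring 960 down to 542 (1 − 542/960) is only a back-calculation.
- **That 542 is wrong in a way that endangers the trial.** The error is on the safe side: 542 exceeds what 80 teams need, so the real margin is larger than stated.

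**Conclusion.** The point holds in a limited form. The stated hypothesis is a treatment-by-history interaction. The named comparison does not test it, and the protocol's inputs do not support using this sample to show a differential effect unless the difference is large: about 0.35 to 0.44 SD with all 960 analysed, or 0.47 to 0.59 SD with 542. Even the smallest of these exceeds the 0.30 SD targeted for the whole intervention.

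These figures rest on the stated ICC and 80 teams, the assumed 20% to 50% history share, and an analysis without baseline adjustment. Adjustment could raise power but is not specified. The 46% to 60% disagreement rate also treats the two subgroup tests as independent.

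It would go too far to say that a power claim is broken or that the main comparison is short of employees. The loose factor of two and the conservative 542 are minor. The protocol's Methods/design section says that team size varies between divisions, and unequal teams would need more than 426, so there is no case for lowering the requirement.

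**What to change.** Replace the sentence on supplementary analyses with text along these lines: *One treatment-by-history interaction, with history taken from the baseline questionnaire, will be estimated in the cluster-adjusted model and reported with its 95% confidence interval. It is exploratory and not powered: for a history share of 20% to 50%, the difference detectable with 80% power is about 0.35 to 0.44 SD if all 960 employees are analysed, and 0.47 to 0.59 SD with 542.* If the sponsor has an expected history share and loss rate, state them and narrow the range. Effects within each group may be shown beside the interaction, but should not be used to judge whether the effects differ.

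As a minor edit, replace the factor of two with the ratio of 1.77. Leave 542 as the requirement.

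The cost is one reworded passage and a less favourable subgroup claim. Sample size, allocation, outcomes and the primary analysis do not change.
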